# The clinical effects of Gyejibongnyeong-Hwan (Gui Zhi Fu Ling Wan) on patients with hyperlipidemia: A study protocol for a multicenter, double-blind, two-armed parallel, investigator-initiated, exploratory randomized controlled trial

**DOI:** 10.1097/MD.0000000000033093

**Published:** 2023-04-21

**Keywords:** dyslipidemia, Gyejibokryeong-Hwan, herbal medicine, hyperlipidemia, Korean medicine, Randomized controlled trial

## Abstract

**Methods::**

This was a 2-armed, parallel, multicenter, and exploratory randomized controlled trial on dyslipidemia. We will recruit 90 patients aged 20 to 65 years with hyperlipidemia between November 2021 and December 2022. Eligible participants will be randomly assigned to receive GBH or placebo granules for 8 weeks and followed up for 4 weeks after 4 weeks of lifestyle modification. The primary outcome is the percentage changes in low-density lipoprotein cholesterol from baseline to week 8. The secondary outcomes are percentage changes in other blood lipid parameters, blood glucose parameters, and blood stasis scores. As an exploratory outcome measure, metabolite analysis will be conducted to observe changes in metabolic patterns.

**Discussion::**

This is the first randomized controlled trial to explore the clinical effect and safety of GBH compared to placebo control in patients with hyperlipidemia, thereby potentially facilitating better management of hyperlipidemia. The results of this pilot study could form a foundation for future large-scale confirmatory clinical trials.

**Ethics and dissemination::**

This study was permitted by the Ministry of Food and Drug Safety on investigational new drug application on August 12, 2021 and approved by the Institutional Review Board of Kyung Hee University, Seoul, Republic of Korea (KOMCIRB202110012001) on November 26, 2021. The results will be published in a peer-reviewed journal and disseminated electronically and in print.

## 1. Introduction

Hyperlipidemia, the most common form of dyslipidemia, involves abnormally elevated levels of lipids in the blood, including cholesterol and triglycerides (TG), and is associated with an increased risk of atherosclerotic cardiovascular (CV) disease.^[1]^

Recently, hyperlipidemia prevalence has been increasing worldwide over the past decades due to factors such as diet, lifestyle, and aging. The prevalence of dyslipidemia in South Korea reached over 38% in 2018, comparable to the prevalence in other countries, and the substantial disease burden has also been increasing consequently.^[2,3]^ Generally, hyperlipidemia has no clinically obvious physical signs or symptoms; it is usually detected through blood tests.

nonpharmacological interventions, such as dietary, exercise, and other lifestyle changes, are recommended for the primary prevention of hyperlipidemia before considering medication. However, if appropriate medication is required in high-risk patients, statins (3-hydroxy-3-methyl-glutaryl-coenzyme reductase inhibitor) are considered first-line agents.^[2]^ Particularly, low-density lipoprotein cholesterol (LDL-C) is a well-known risk factor for coronary artery disease and a major lipid indicator that determines the risk assessment and treatment principle of CV disease.^[4]^ In actual clinical and treatment guidelines, the primary treatment goal for dyslipidemia is to set the LDL-C target level according to the presence or absence of CV disease and its risk, and statin treatment is widely prescribed as the primary treatment for lowering LDL-C levels. However, significant residual CV risk has been noted in several trials of statin therapy, and consequently, there has been increased interest in modulating nonLDL-C levels, such as TG and HDL-C levels, to achieve further reduction in residual CV risk during statin treatment.^[5]^ In addition, in the case of statin drugs, side effects such as digestive disorders, heartburn, liver toxicity, rhabdomyolysis, and diabetes remain a concern.^[6–8]^ Therefore, there is a constant demand for a therapeutic agent with relatively good efficiency and few side effects that can be administered from the initial stage of hyperlipidemia. Herbal medicines derived from natural products can be considered an option for treating dyslipidemia.

In traditional East Asian medicine, hyperlipidemia is regarded as the retention of phlegm and fluid disease, having similar etiology and pathogenesis based on spleen-deficiency and phlegm-stagnation, accumulation and stasis of heat, and qi and blood stagnation induced by phlegm-damp, water-dampness, and blood stasis. Therefore, strengthening the spleen, dissolving phlegm, clearing away heat and diuresis, supplementing qi, and activating blood circulation are commonly used therapeutic methods for hyperlipidemia.^[9–13]^

In Korea, (Gyejibongnyeong-Hwan [GBH]; Gui Zhi Fu Ling Wan in traditional Chinese; and Keishibukuryogan in Kampo medicine) is an herbal medicine comprising 5 herbs, including *Cinnamomum cassia* Blume, *Poria cocos* Wolf, *Paeonia suffruticosa* Andrews, *Prunus persica* Batsch, and *Paeonia lactiflora* Pallas, widely used to treat several symptoms of blood stasis, which collectively refers to pathological conditions of blood circulation disorder in clinics.^[14,15]^ It has been reported to have antilipid, antiplatelet, antithrombotic, and antiatherosclerosis.^[14]^ In particular, a significant number of preclinical and clinical studies have been reported that have identified the blood lipid-lowering effects of GBH.^[14]^

However, few clinical studies have evaluated the effects of GBH in patients with dyslipidemia in Korea. In other studies, the target lipid parameters of GBH, such as total cholesterol (TC), TG, and LDL-C, have been reported differently according to clinical studies.^[16–21]^

Therefore, this study aims to evaluate the clinical effect and safety of GBH on serum lipid levels and CV risk in patients with borderline hyperlipidemia.

## 2. Methods

### 2.1. Study design and setting

This is a study protocol for multi-center, randomized, double-blind, placebo-controlled, parallel, investigator-initiated pilot study. Subjects will be recruited from 2 hospitals, Kyung Hee University Oriental Medical Center (Seoul) and Wonkwang University, Gwangju Medical Center (Gwangju), between November 2021 and December 2022. The study period will include 4 weeks of lifestyle modification, 8 weeks of medication, and 4 weeks of follow-up. The study period procedure is summarized in the Consolidated Standards of Reporting Trials (CONSORT) diagram (Fig. 1), and the schedule of enrollment, intervention, and assessments is summarized in Table 1. The trial will be performed in accordance with the Declaration of Helsinki and the Good Clinical Practice Guidelines. This study was sponsored and managed by the Korea Institute of Oriental Medicine (KIOM) during the study period. KIOM wrote the protocol following the CONSORT Extension for Chinese Herbal Medicine Formulas 2017^[22]^ and Standard Protocol Items: Recommendations for Interventional Trials 2013 statement.^[23]^

**Table 1 T1:** Schedule of enrollment, interventions, and assessments.

	Study period					
	Screening		Post allocation			Follow-up
Time point	1st (−4 w)	2nd (±7 d)	Baseline (−14 d)	W 4 (±7 d)	W 8 (±7 d)	W 12 (±7 d)
Enrollment						
Informed consent	●					
Eligibility screen	●					
Demographic characteristics	●					
Medical history	●					
Random allocation			●			
Interventions						
Dietary and exercise education	●	●	●	●	●	
GBH or placebo			← - - - - - - - - - - - - - - - - - - - - →			
Assessments						
Vital sign	●	●	●	●	●	●
Laboratory testing*	●	●		●	●	●
Pregnancy testing		●		●		
Blood stasis questionnaire	●		●		●	
Blinding test					●	
Adverse events			●	●	●	●
Medication compliance				●	●	

GBH = Gyejibongnyeong-Hwan.

* Including hematological test, blood lipid parameters, blood glucose parameter, liver and renal function test, and urine test.

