### 2.3. Eligibility criteria

#### 2.3.1. Inclusion criteria.

Adults aged 19 years or over but under 65 years.Eligible subjects through screening tests and whose lipid profile results after 4 weeks of lifestyle modification correspond to 1 or more of the following: (a) TC ≥ 200 mg/dL, (b) TG 150 to 499 mg/dL, (c) LDL-cholesterol 130 to 250 mg/dL, and (d) HDL-cholesterol < 40 mg/dL (However, even if the subject corresponds to more than 1, LDL-cholesterol should not exceed 250 mg/dL, and TG should not exceed 499 mg/dL).Voluntary signed written informed consent after sufficient explanation of this study.

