### 2.5. Interventions

Before allocation into groups, all participants will be educated and instructed to follow dietary and exercise guidelines for hyperlipidemia using a brochure based on the Guidelines by the Korean Ministry of Food and Drug Safety for clinical trials for hyperlipidemia treatment for 4 weeks.^[24]^ After 4 weeks of lifestyle modification, eligible participants will be randomly assigned to receive GBH or placebo granules for 8 weeks. GBH, a light brown granular substance, will be prepared by Hanpoong Pharm and Foods Co., Ltd. (Batch number: 20001; Wanju, Jeollabuk-do, South Korea). It will be produced according to the Korean Good Manufacturing Practice guidelines outlined by Korea Ministry of Food and Drug Safety and manufactured so that there is no difference between them in shape, color, smell, or taste. A blinded pharmacist will check the storage, dispensation, and quality of the investigational products. GBH is made of an extract comprising the following herbs: *Cinnamomum cassia* Blume (1.33 g), *Poria cocos* Wolf (1.33 g), *Paeonia suffruticosa* Andrews (1.33 g), *Prunus persica* Batsch, and *Paeonia lactiflora Pallas* (1.33 g), which were extracted with 8 to 10 times the volume of water at 80°C to 100°C for 2 to 3 hours. The extract was filtered, and the filtrate was concentrated under reduced pressure at 60°C or lower to obtain the herbal extract. The placebo granule was made of corn starch, lactose hydrate, hydroxypropyl methylcellulose, Opadry® 200, and caramel coloring.

Participants will be instructed to take 1 pack (4.0 g) 3 times daily for 8 weeks. The dosage regimen is based on an authorization from the Korean Ministry of Food and Drug Safety. Participants will be instructed to return unopened packages of the investigational product to check their adherence to the treatment. If any adverse events occur, investigators will take appropriate action depending on the severity of the adverse event and its causal relationship with the investigational product.

Co-administration of medications used for managing metabolic diseases, such as hypertension and diabetes, and dietary supplements that do not directly affect hyperlipidemia can be permitted during the study period. However, participants will be instructed not to change the dose or type of concomitant medication as much as possible, if they are changed, and the investigators will record the details in the case report form (CRF).

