### 2.6. Outcomes measures

#### 2.6.1. Primary outcome.

Percentage changes in LDL-C from the baseline to week 8.

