### 2.9. Randomization and allocation concealment

An independent statistician will generate a random assignment code using the block randomization method with block sizes in SAS® Version 9.4 (SAS Institute Inc., Cary, NC). Participants who satisfy the eligibility criteria will be assigned to the GBH or placebo granule group at the baseline visit (week 0) with a 1:1 allocation ratio. The generated code will be sealed in opaque envelopes and stored in double-locked cabinets. We will maintain allocation concealment throughout the study period by providing participants with identically packaged, consecutively numbered drug containers.

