### 2.12. Statistical analysis

An independent statistician will conduct statistical analysis using SAS® Version 9.4 (SAS Institute Inc., Cary, NC). According to principle, an efficacy analysis will be conducted using a full analysis set according to the intention-to-treatment principle, including all randomly assigned participants who received at least 1 evaluation after the investigational product has been prescribed at least once. If necessary, per-protocol set analysis will also be conducted, including only participants who have completed the entire process as described in the protocol and have no significant violations. Participants with < 70% compliance with the investigational product will be excluded from the per-protocol set analysis. The safety analysis will include all data obtained from participants who have taken at least 1 investigational product.

The demographic and general clinical characteristics of the participants will be summarized by grouping. Continuous data will be presented as mean and 95% confidence intervals or medians according to the data distribution, and dichotomous data as frequency and percentage. Continuous data will be analyzed using the independent t-test or Wilcoxon rank-sum test, and dichotomous data will be analyzed using the chi-square test or Fisher exact test.

The primary outcome of this study is the mean change in LDL-C levels from baseline to week 8. A 2-sided test with a significance level of 5% will be performed using an analysis of covariance with baseline as the covariate and the treatment group as the fixed factors. The intragroup changes in outcome measures from baseline to posttreatment will be analyzed using the paired *t* test or Wilcoxon signed-rank test for continuous variables and the chi-square test or Fisher exact test for dichotomous variables. Furthermore, repeated-measures analysis of variance will be used to compare the differences in trends between visits in each group. Missing values will be replaced with the multiple imputation method. If necessary, subgroup analysis can be performed by categorizing the initial characteristics of participants at the screening or baseline visit.

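### Table 1 schedules no lipid test at the Baseline visit, so which pre-treatment LDL-C is the baseline is not fixed, and the earlier value goes unused

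*Protocol article*

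**What the plan says.** The relevant statements are spread over five places in the protocol article.

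- **Section 2.1, Table 1.** The row "Laboratory testing" is marked at the 1st screening, the 2nd screening, week 4, week 8 and week 12. The Baseline cell is empty. The footnote lists what the row covers: "Including hematological test, blood lipid parameters, blood glucose parameter, liver and renal function test, and urine test". Lipids, and so LDL-C, fall under it.
- **Section 2.6.1.** The primary outcome is "Percentage changes in LDL-C from the baseline to week 8".
- **Section 2.9.** Participants "will be assigned to the GBH or placebo granule group at the baseline visit (week 0) with a 1:1 allocation ratio". The baseline visit is therefore week 0, the point of randomisation.
- **Section 2.12.** "A 2-sided test with a significance level of 5% will be performed using an analysis of covariance with baseline as the covariate". The same section plans intragroup tests of change from baseline to post-treatment.
- **Sections 2.3.1 and 2.5.** Eligible participants are those "whose lipid profile results after 4 weeks of lifestyle modification correspond to 1 or more of the following", and the order of events is given as "After 4 weeks of lifestyle modification, eligible participants will be randomly assigned to receive GBH or placebo granules for 8 weeks".

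No sentence says which blood sample supplies the baseline LDL-C.

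**The concern.** Baseline LDL-C enters the primary analysis twice: as the starting point of the change and as the covariate. The one pre-treatment visit called Baseline is the one at which no lipids are scheduled. The article does not treat screening and baseline as the same thing. Table 1 marks the blood stasis questionnaire at both the 1st screening and Baseline, and Section 2.12 names the two visits separately when it describes subgroups.

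The two candidate samples mean different things. The 1st-screening value precedes the dietary and exercise run-in, so a change measured from it spans about 12 weeks and includes the run-in. The 2nd-screening value follows the run-in and measures what the outcome is meant to measure. The choice matters most for the within-arm changes and their planned tests. The same gap affects the secondary lipid outcomes in Section 2.6.2.

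There is also an unused resource: a second pre-randomisation LDL-C is scheduled for every participant and appears nowhere in the analysis.

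**Working it through.** **1. Reading the schedule.** Laboratory row of Table 1, by column:

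| Visit | 1st screening | 2nd screening | Baseline | W4 | W8 | W12 |
|---|---|---|---|---|---|---|
| Laboratory testing | yes | yes | no | yes | yes | yes |

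This gives two LDL-C values before treatment and none at the visit labelled Baseline.

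**2. Is there a usable baseline?** Section 2.3.1 requires lipid results after the run-in, Section 2.5 places randomisation after the run-in, and Table 1 has a laboratory mark at the 2nd screening. Together these give every randomised participant an LDL-C taken after the run-in and before treatment.

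**3. Effect of the choice on the reported changes.** Assumptions (none is in the article): a run-in fall of L between the two screenings in both arms, a GBH effect of r = 10% after the 2nd screening, and no placebo effect.

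- Change from 2nd screening: -r in the GBH arm, 0 in the placebo arm.
- Change from 1st screening: (1 - L)(1 - r) - 1 in the GBH arm, -L in the placebo arm.
- Arm difference from 1st screening: (1 - L) × r.

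| L | From 2nd: GBH / placebo | From 1st: GBH / placebo | Difference from 2nd | Difference from 1st |
|---|---|---|---|---|
| 0% | -10.0% / 0.0% | -10.0% / 0.0% | 10.0 | 10.0 |
| 5% | -10.0% / 0.0% | -14.5% / -5.0% | 10.0 | 9.5 |
| 10% | -10.0% / 0.0% | -19.0% / -10.0% | 10.0 | 9.0 |

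For L = 5%: 0.95 × 0.90 = 0.855, hence -14.5%. The within-arm changes shift by about the size of the run-in effect. The contrast shrinks only by the factor 1 - L.

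**4. Time covered by the change.** From a week-0 sample, week 8 with its 7-day window spans 56 - 7 = 49 to 56 + 7 = 63 days. If the -14 d under Baseline means up to 14 days after the 2nd screening, the interval from that sample spans 49 to 63 + 14 = 77 days. Table 1 does not say what the -14 d is counted from, so the 77 is conditional on that reading. From the 1st screening the nominal interval is 28 + 56 = 84 days.

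**5. Value of the second covariate.** Assume equal pairwise correlation ρ among 1st-screening, 2nd-screening and week-8 LDL-C. Residual variance of the week-8 value, as a share of its total variance, is 1 - ρ² with one pre-value and 1 - 2ρ²/(1 + ρ) with two.

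| ρ | One pre-value | Two pre-values | Reduction |
|---|---|---|---|
| 0.6 | 0.640 | 0.550 | 14% |
| 0.7 | 0.510 | 0.424 | 17% |
| 0.8 | 0.360 | 0.289 | 20% |

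Cross-check: the reduction equals the squared partial correlation, here (ρ/(1 + ρ))². For ρ = 0.6 this is 0.375² = 0.141; for ρ = 0.8 it is 0.444² = 0.198.

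Confidence intervals narrow by a factor between √0.859 = 0.93 and √0.802 = 0.90, that is by about 7% to 10%. The figures are for the week-8 value or the absolute change adjusted for baseline, and are approximate for percentage change.

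Equal correlation is favourable to the claim. If the correlation of the 1st screening with week 8 is only the product of the two adjacent correlations, the partial correlation is zero and the gain vanishes.

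**6. Cost.** Section 2.8 gives 45 per arm with 20% dropout, so 45 × 0.8 = 36 per arm and 72 evaluable. Residual degrees of freedom go from 72 - 3 = 69 to 68.

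**The case against.** The strongest reply is that the schedule is deliberate and its meaning plain. Lipids and the pregnancy test are placed at the 2nd screening because results are needed before allocation, while the questionnaire needs no laboratory turnaround and can be done at Baseline. Most analysts would take the 2nd-screening value without being told. The article condenses a fuller protocol, its flow chart is not shown here, and a sentence naming the baseline sample may well stand elsewhere. Much of this is right, and it limits the point to a mismatch between the schedule's label and the primary analysis.

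Four stronger readings are tempting and are not supported:

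- *That no baseline LDL-C exists.* Table 1 and the eligibility rule together provide one.
- *That the treatment comparison is biased.* Both candidates precede randomisation and would be applied alike in two blinded arms. Using the eligibility value as baseline brings regression to the mean into both arms' changes, but not into the contrast.
- *That different participants would be measured from different visits.* Both samples are scheduled for everyone, and nothing suggests mixing them.
- *That the primary test will be picked from two analyses.* An unnamed baseline leaves that open in principle, but nothing in the article points to it.

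It is also fair to say that ANCOVA with one baseline is sound. The second covariate is an efficiency gain, not the repair of an error, and its size does not measure the labelling problem.

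**Conclusion.** The point holds in a limited form. The visit defined as baseline has no lipid test, the primary outcome and covariate both rely on a baseline LDL-C, and the article does not say which of two available values is meant. The 2nd-screening value is usable and is the natural choice, so the randomised comparison stands. Under the assumed 10% effect and 5% run-in fall, the wrong choice would move the arm difference by 0.5 points, but would move the within-arm changes by 4.5 (GBH) and 5.0 (placebo) points and distort the planned intragroup tests.

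The larger practical gain lies in the unused 1st-screening value: 14% to 20% less residual variance if pairwise correlations are equal at 0.6 to 0.8, and less, possibly close to nothing, if the earlier value is only weakly related to week 8. These correlations and the run-in effect are assumptions; the article gives neither. Severity is minor to moderate for an exploratory trial.

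**What to change.** Before unblinding:

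1. State that baseline for every laboratory outcome, in both the change and the covariate, is the 2nd-screening value. If a week-0 pre-dose sample was intended, mark it in the Baseline column of Table 1 and use that value instead.
2. Say what the -14 d under Baseline is counted from.
3. Add the 1st-screening LDL-C to the primary ANCOVA as a second covariate, alongside baseline and treatment group.

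The first two items cost a sentence each, with no new blood sample if the 2nd-screening value is used. A week-0 baseline needs one draw per participant. The third uses data already scheduled for everyone before randomisation. It introduces no bias and costs one of about 69 residual degrees of freedom.

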**Figure 1. F1:**
[figure not shown]
Study flow chart. GBH, Gyejibongnyeong-Hwan.

### 2.2. Study registration

This study is registered with the Clinical Research Information Service (https://cris.nih.go.kr/cris/en/) (KCT0006842). The current protocol versions are 1.1.

### 2.3. Eligibility criteria

#### 2.3.1. Inclusion criteria.

Adults aged 19 years or over but under 65 years.Eligible subjects through screening tests and whose lipid profile results after 4 weeks of lifestyle modification correspond to 1 or more of the following: (a) TC ≥ 200 mg/dL, (b) TG 150 to 499 mg/dL, (c) LDL-cholesterol 130 to 250 mg/dL, and (d) HDL-cholesterol < 40 mg/dL (However, even if the subject corresponds to more than 1, LDL-cholesterol should not exceed 250 mg/dL, and TG should not exceed 499 mg/dL).Voluntary signed written informed consent after sufficient explanation of this study.

